### 10.3.3 Assessment of Seriousness

Determination of the seriousness of the adverse event according to the definitions for a serious adverse event (SAE) given in section 10.2.6.

### 10.3.4 Assessment of Causality

Causality (likelihood that the event is related to the study agent) will be assessed considering the factors listed under the following categories:

#### Definitely Related

- reasonable temporal relationship
- follows a known response pattern
- clear evidence to suggest a causal relationship
- there is no alternative etiology

#### Probably Related

- reasonable temporal relationship
- follows a suspected response pattern (based on similar agents)
- no evidence of a more likely alternative etiology

### **Possibly Related**

- reasonable temporal relationship
- little evidence for a more likely alternative etiology

### **Unlikely Related**

- does not have a reasonable temporal relationship
- OR
- good evidence for a more likely alternative etiology

### **Not Related**

- does not have a temporal relationship
- OR
- definitely due to an alternative etiology

## **10.4 Adverse Event Recording**

Any AE relevant for the evaluation and analysis of the clinical trial has to be documented in the source data and in the CRF on the respective Adverse Event Report Form.

Documentation and evaluation of each AE occurring between:

- Visit 3 (first day of treatment) and
- Visit 5 (4 months follow-up)

## **10.5 Adverse Event Reporting**

Line listings, frequency tables, and other summary AE data will be submitted to the Sponsor when needed for periodic safety assessments requested by the DSMC, review of annual reports, review of safety reports, and preparation of final study reports.

## **10.6 Serious Adverse Event Reporting**

### **10.6.1 Serious Adverse Event Reporting**

Any SAE (whether or not they are also UPs) occurring after the subject has received the trial drug for the first time until the 2 months follow-up (Visit 4) will be documented and reported within 48 hours after investigator awareness of the event to the Ghana FDA, the GHS and to the Sponsor informally via email containing at least the minimal criteria (the name of the clinical trial, an identifiable patient, an identifiable reporter, a reaction/event, a causality assessment). The Sponsor will add missing information in consultation with the investigator and submit the completed SAE form to the FDA and the GHS.

FDA: [contact]

GHS: [contact]

## **10.7 Reporting of Unanticipated Problems (UPs)**

Unanticipated Problems (definition see chapter 10.2.9) that are also adverse events must be reported to the Sponsor and sent by fax or e-mail attachment no later than 7 calendar days of site awareness of the event. UPs that are not AEs are not reported to the Sponsor.

## 10.8 Follow-up of Adverse Events

Every AE or SAE will be treated according to clinical standards at the discretion of the investigator and followed up until it is resolved. Costs for treatment of AEs/SAEs will be covered by the research team.

## 10.9 Handling of emergency cases

The study clinicians/physicians will visit the participants in their villages every day during the treatment period to closely supervise possible AEs or SAEs. Additionally the phone numbers of the trial clinicians will be handed to the village health workers as well as to the participants. In case of an emergency between the visits, the clinicians have to be called and will come to the participants whenever needed. In case the participant has to go to a hospital for further examinations and treatment, the transport and medical care will be paid by the research team.

## 10.10 Deaths

All fatal cases during the treatment period and the time of follow-ups will be accompanied by a formal autopsy report. Deaths occurring in the period between treatment and follow-ups will be evaluated in detail and, if reported immediately to the research team, also accompanied by a formal autopsy.

## 10.11 Pregnancies

Female participants will be screened for pregnancy before enrolment. Pregnant and/or breastfeeding women will be excluded because doxycycline is contraindicated in pregnancy and during breastfeeding. However, non-pregnant women of childbearing-potential using an approved, effective method of contraception before, during and for at least 2 weeks after the completion of the active intervention with doxycycline or placebo are eligible for inclusion. As doxycycline is reducing the blood level of contraceptives it is recommended to use an additional method (barrier) to prevent a pregnancy during the treatment phase with doxycycline.

Approved methods of contraception such as implants, intrauterine device (IUD), condoms etc. which are practiced in Ghana would be used.

### 10.11.1 Pregnancy Procedures

Women of childbearing potential are required to have a negative urine pregnancy test to exclude a pregnancy before being enrolled in the clinical trial.

Pregnancy testing will be conducted prior to the first dose of the trial drug and will be repeated after 2, 4 and 6 weeks of treatment.

All women of childbearing potential will be instructed to contact the investigator immediately if they suspect they might be pregnant during the study (for example, missed or late menses). If pregnancy is suspected while the patient is receiving experimental study treatment, this will be withheld immediately until pregnancy can be ruled out with certainty.

If a woman becomes pregnant during the treatment period, treatment with the IMP will be immediately stopped. She will be treated according to clinical routine at the discretion of the treating medical doctor supported by the investigator. The woman will remain in the trial as a participant (Intention-to-treat collective).

### 10.11.2 Pregnancy Reporting

To ensure the safety of female subjects, each pregnancy that becomes known to the investigator during the trial, must be reported as an event similar to an SAE. Therefore the investigator will record and

report pregnancy information on the appropriate pregnancy report form as an initial report and send it immediately (latest within 24h) to the Sponsor.

The pregnancy itself is not considered to be an AE or SAE but must be followed up until delivery or until pregnancy termination and the outcome of pregnancy should be notified to the Sponsor to determine the outcome of the pregnancy regarding maternal or newborn complications. The investigator will seek and provide this follow-up information after the planned date of delivery. For this purpose the pregnancy report form will be used as follow-up report. Infants should be followed for a minimum of 12 months after delivery.

If the outcome of the pregnancy includes

- Spontaneous, therapeutic abortion or voluntary termination,
- stillbirth,
- neonatal death,
- presence of birth defects, or
- congenital anomaly (including that in an aborted fetus, stillbirth or neonatal death),

the investigator should report this outcome as an SAE.

## 11. STATISTICAL CONSIDERATIONS

### 11.1 Hypothesis

Doxycycline is superior to placebo for management of lymphedema in patients from LF-endemic areas.

### 11.2 Primary target variable

Lack of progression of LE (stage reduction or same stage as pre-treatment) examined 24 months after treatment onset.

### 11.3 Sample size estimations

#### 11.3.1 Sample size estimations for group A (LE stage 1-3)

- Doxycycline 200mg/d will first be tested for superiority to placebo. When superiority of doxycycline 200mg/d is confirmed, doxycycline 100mg/d will subsequently be tested for superiority to placebo. If both treatment groups rejected their  $H_0$ -hypothesis, they will be tested for non-inferiority. With this subsequent design, a two-sided  $\alpha = 5\%$  can be maintained for all 3 analyses.
- The estimates for progression are based on the results from the previous study by Mand et al. [2] where a progression of 4.9% was seen in the DOX 200 group after 24 months whereas the placebo-treated patients had a progression of 55.6%. The strict control implementation of hygiene measures in this trial may result in a stronger impact of this intervention on both arms. This would result in a smaller margin to verify the added benefit of doxycycline and as a consequence increase the number of patients in the study. In order to account for this influence in the sample size calculations the progression in the placebo group was assumed to be 25% instead of 55%.
- A dropout rate of 30% was assumed.

### 11.3.2 Sample size estimations for group B (LE stage 4-6)

- Doxycycline 200mg/d will first be tested for superiority to placebo with  $\alpha=5\%$  two-sided.
- Since the previous trial [2] was mainly carried out in patients with LE stages 1-3, the results cannot be used as basis for a sample size calculation for the LE-stages 4-6. Therefore a sample size was chosen for this part which is in line with the sample sizes normally taken for pilot trials.
- A dropout rate of 30% was assumed.

## 11.4 Sample size calculation

### 11.4.1 Sample size calculation for group A (LE stage 1-3)

Based on the assumption of a progression in the DOX 200 group of 5% and in the placebo group of 25%, there will be power of 95% to show superiority to placebo if 84 participants are included in each treatment group (+ 30% drop-out rate:  $N = 120/\text{treatment}$ ). Using the subsequent design, superiority of DOX 100 to placebo can be shown with a power  $> 81\%$  if the progression in this group is  $\leq 8\%$ .

### 11.4.2 Sample size calculation for group B (LE stage 4-6)

Since this part of the trial is a non-confirmatory pilot study to gain experience with doxycycline in the treatment of higher LE stages, the sample size cannot be justified by a statistical argumentation. Therefore a sample size of 30 participants ( $N = 21 + 30\%$  drop-out rate) per treatment arm was chosen which is in line with the sample sizes normally taken for pilot trials.

## 11.5 Achievement of sample size

The clinical centers involved in the study were selected based on documentation for patient availability and availability of infrastructure and resources for the study (see 7.4.1 and 7.4.2).

## 11.6 Populations to be analyzed

Different analysis populations will be prepared before de-blinding (Safety population (SAF), Intention-to-treat population (ITT), Per-Protocol population (PP)). The criteria for the exclusion of patients from any of the analysis populations will be defined in the Statistical Analysis Plan (SAP) and will be finalized prior to database lock. The exclusion of participants from the analysis populations will then be decided during the blind data review before unblinding and will be described in detail in the blind data review report.

Since this is a superiority trial the ITT population will be used for all endpoint analyses. The PP population will be used to confirm the results of the ITT analysis. The SAF population will be used for the analysis of adverse events.

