| Statistical Rationale         | 
Statistical analyses will be done first “intention to treat” (ITT) followed by “per protocol” (PP) to confirm the results.
 
Primary statistical Analysis:
 
The frequencies of the participants with “progression” and their confidence intervals (95%) will be calculated and compared between the treatment groups using Fisher’s exact test.
 
For group A: Superiority to placebo has to be proven for DOX 200 before testing superiority to placebo for DOX 100. If both tests show superiority to placebo with <math>\alpha = 0.05</math>, non-inferiority of DOX 100 to DOX 200 can be tested in a final step.
 
For group B: DOX 200mg/d will be tested for superiority to placebo with an <math>\alpha</math>-level of 5%.
 
Secondary Endpoints:
 
Secondary endpoints will be described as estimators with confidence intervals (95%) for each intervention group and analyzed with adequate statistical methods.
 
Safety Analysis:
 
Frequency of Adverse events and Serious Adverse Events will be analyzed. In this analysis all patients will be included who took the drugs at least for one day.
 |
| Trial procedures              | 
There will be 15 visits in total (see schedule of activities):
 
Visit 1: Screening
 
Visit 2: Baseline
 
Visit 3: Treatment (42 days)
                                                                                                                                                                                                                                                                                                                                                                                                                                                                                                                                                                                                                                                                                                                                                                                                                                                                                                                                                                                                                            |

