## 6. STUDY OBJECTIVES

### 6.1 Primary Objectives

Group A (LE stage 1-3):

- to confirm the efficacy of a 6-week course of daily doxycycline 200mg on lack of progression of filarial LE
- to reduce the dosage of doxycycline from 200mg/d to 100mg/d for 6 weeks for the treatment of filarial LE

Group B (LE stage 4-6):

- to show efficacy of a 6-week course of daily doxycycline 200mg on lack of progression of filarial LE

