### 11.6.1 Intent-to treat (ITT) population

The ITT population will consist of all randomized patients in the groups to which they were randomly assigned and who took the study drugs at least once.

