### 11.7.2 Analysis of the primary endpoint

The frequencies of the participants with “progression” and their confidence intervals (95%) will be calculated and compared between the treatment groups using Fisher’s exact test.

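### The superiority premise behind the ITT rule, and Fisher's exact test, do not cover the planned non-inferiority step of DOX 100 against DOX 200

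*Protocol*

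**What the plan says.** Four parts of the protocol bear on this.

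- **Trial type and analysis set.** Section 11.6: "Since this is a superiority trial the ITT population will be used for all endpoint analyses". On the per-protocol (PP) set it adds: "The PP population will be used to confirm the results of the ITT analysis". Section 11.6.1 restricts ITT to randomized patients "who took the study drugs at least once". The hypothesis in section 11.1 concerns placebo only: "Doxycycline is superior to placebo for management of lymphedema in patients from LF-endemic areas".
- **The third test.** For group A, section 11.3.1 tests DOX 200 against placebo, then DOX 100 against placebo. If both null hypotheses are rejected, "they will be tested for non-inferiority". It claims a two-sided 5% level for all three analyses. The synopsis is softer: "non-inferiority of DOX 100 to DOX 200 can be tested in a final step".
- **Its purpose.** One of the two primary objectives for group A (section 6.1) is "to reduce the dosage of doxycycline from 200mg/d to 100mg/d for 6 weeks for the treatment of filarial LE".
- **The method.** Section 11.7.2 gives each arm's progression frequency a 95% confidence interval, and the frequencies are "compared between the treatment groups using Fisher’s exact test". The synopsis says the same. Section 11.4.1 gives power for the two placebo comparisons and none for the dose comparison.

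**The concern.** The ITT rule is derived from a description of the trial that is true of two group A tests and untrue of the third. The third is no side analysis: it sits in the alpha-controlled sequence and answers a primary objective.

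ITT is preferred for superiority because dilution from missed treatment works against the claim. In a non-inferiority comparison of two active arms, the same dilution can make the arms look alike and so help the claim. A test of equality has a related weakness: it contains no margin, and failure to reject is weaker evidence the smaller the trial. A statistical analysis plan that obeys section 11.6 has to make ITT the deciding set for non-inferiority; one that does not will contradict the protocol. At stake is whether the dose-reduction conclusion rests on a valid decision rule.

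**Working it through.** **Inputs.** From section 11.4.1: 84 evaluable per arm; progression 5% on DOX 200, 25% on placebo, 8% on DOX 100. From section 11.3.1: two-sided 5% level, 30% drop-out. The true DOX 100 rates of 12% and 15%, and every margin below, are assumptions made here.

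**1. The plan's own figures.** The exact power of Fisher's test sums Bin(x; 84, p₁) × Bin(y; 84, p₂) over all pairs (x, y) with p ≤ 0.05.
- 5% against 25%: 95.5% (stated: 95%).
- 8% against 25%: 81.4% (stated: above 81%).
- 84 / (1 − 0.30) = 120 per arm, as stated.

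The sample size is therefore correct, and it is built on the two superiority tests alone.

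**2. Why Fisher's test cannot carry the third step.** Take 4/84 progressing on DOX 200 and 10/84 on DOX 100. Fisher's p = 0.16, so no difference is declared. The Newcombe upper limit for the excess on DOX 100, with Wilson limits u₁ (DOX 100, upper) and l₂ (DOX 200, lower), is

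p₁ − p₂ + √[(u₁ − p₁)² + (p₂ − l₂)²]
= 0.0714 + √[(0.2055 − 0.1190)² + (0.0476 − 0.0187)²] = 0.163.

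The same data are compatible with about 16 more progressions per 100 patients. The 95% intervals in section 11.7.2 do not supply this limit, because they describe each arm separately and not the difference.

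**3. How often a non-significant result would arise.** All three arms were enumerated together at 84 each. The sum runs over outcomes in which DOX 200 beats placebo, DOX 100 beats placebo, and DOX 100 against DOX 200 has p > 0.05.

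| True DOX 100 progression (DOX 200: 5%) | Dose comparison non-significant, taken alone | Same, and both placebo tests succeed |
|---|---|---|
| 12% | 72% | 43% |
| 15% | 49% | 22% |

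The last column is the relevant one, because the hierarchy allows the third step only after the first two. At 15%, DOX 100 beats placebo in only about 30% of trials. Under a Newcombe rule with an illustrative 10-point margin, the last column would fall to about 9% and 2%.

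**4. Power of a proper third step.** Probability that the Newcombe 95% upper limit lies below the margin at the plan's own 5% against 8%:

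| Assumed margin | Power |
|---|---|
| 5 points | 6% |
| 10 points | 41% |
| 15 points | 81% |

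At 10 points, the probability that both placebo tests and non-inferiority all succeed is 37%.

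**5. The analysis sets.** ITT takes in anyone dosed once (section 11.6.1), and drop-outs contribute all available data (11.10.3). PP drops those missing more than three consecutive treatment days (11.10.4). No section makes the non-inferiority claim depend on PP. PP would also leave one source of similarity in place: under section 9.3, participants below 50 kg in the DOX 200 arm take one 100 mg tablet, the same active dose as in the DOX 100 arm.

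**The case against.** Several points on the other side are sound.

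- **No decision rule based on non-significance is written.** A reader might infer that a non-significant Fisher result will be taken as non-inferiority. The protocol says nothing of the kind: it announces a non-inferiority test and gives no method for it. This stands, so the 22% and 43% show the cost of one possible reading and not of a stated rule.
- **The unconditional 49% and 72% overstate the risk.** They ignore the two placebo tests that must succeed first. This stands.
- **The margin and interval method may be in the statistical analysis plan.** Section 11.7 promises a detailed plan before de-blinding, with agreement of the monitoring committee. This stands: their absence from the protocol is not the finding.
- **PP is not absent.** It is required as confirmation, and a discordant PP result would be visible. This stands in part: confirmation is not equal standing, and nothing says what follows if the sets disagree.
- **The direction of bias in ITT is not certain.** Drop-outs without a month-24 stage might simply not contribute, and that could bias either way. Observed dosing and the extension for missed days (11.9) limit dilution. This stands against any claim that ITT must favour non-inferiority. It does not make ITT the conservative set, which is what the reasoning in 11.6 needs.
- **The step is last, conditional, and only possible in the synopsis wording.** True, but section 11.3.1 says the test will be done, and it serves a primary objective.

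**Conclusion.** The protocol is wrong as written on a narrow point. Section 11.6 applies a superiority rationale to all endpoint analyses although a confirmatory non-inferiority test is among them, and the only between-arm method named for the primary endpoint cannot perform that test. This is a contradiction within the protocol, so it cannot be put down to detail left for the statistical analysis plan.

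The size depends on a reading the protocol does not state. If non-significance were taken as non-inferiority, a DOX 100 arm with 15% true progression against 5% would pass all three steps in about 22% of trials, and one with 12% in about 43%. These figures assume 84 evaluable per arm and 25% progression on placebo.

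The documents do not support the stronger conclusions that the plan will endorse a worse dose, that no margin exists, or that the trial is undersized for its superiority tests. Those two tests are correctly sized.

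**What to change.** 1. In section 11.6, limit the superiority and ITT sentence to the comparisons with placebo. In section 11.7.2 and the synopsis, limit Fisher's test in the same way.
2. For the third step, add wording such as: *Non-inferiority of DOX 100 to DOX 200 is concluded only if the upper limit of the two-sided 95% confidence interval (Newcombe or Miettinen-Nurminen) for the difference in progression, DOX 100 minus DOX 200, lies below the margin in both the ITT and the PP set.*
3. Justify the margin clinically and fix it before any unblinded look, including the 12-month interim analysis in section 11.8. No particular margin is proposed here.
4. In section 11.4.1, state the power of this step at the chosen margin, alone and jointly with both superiority tests.
5. Align the synopsis and section 11.3.1 on whether the test can or will be done.

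The cost is wording in the protocol, with the analysis plan brought into line. The price is a stricter claim that is harder to win: at the planned 5% against 8%, power may prove low unless the justified margin is wide. The two superiority tests and the sample size for them are unaffected.

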### 11.6.1 Intent-to treat (ITT) population

The ITT population will consist of all randomized patients in the groups to which they were randomly assigned and who took the study drugs at least once.

### 11.6.2 Per-Protocol (PP) population:

The PP population will consist of all patients who fulfil the protocol in terms of eligibility, compliance, interventions, and outcome assessment without any major protocol deviation.

### 11.6.3 Safety Population

The safety population will be defined as all patients who received any study drug

## 11.7 Statistical methodology

A detailed statistical analysis plan (SAP) will be written before final closure of the data file and before de-blinding of the research team. The Data Safety Monitoring Committee (DSMC) will have to agree on the data analysis plan before closure.

### 11.7.1 Analysis of baseline characteristics

Baseline characteristics, such as demographic and analytical data will be summarized for each intervention group using descriptive statistical methods.

